###### 6.3.1.1.2 Adverse Reactions (ARs)

Adverse reactions (ARs) include all untoward and unintended responses to an IMP related to any dose administered. All AEs judged by either the reporting Investigator or the Sponsor as having a causal relationship of possibly, probably or definitely related to the IMP qualify as ARs. An AR is defined as unexpected when its nature, severity or outcome is not consistent with the information that has been obtained from previous observations and investigational trials.

###### 6.3.1.1.3 Serious Adverse Events (SAEs)

A SAE is any untoward medical occurrence that at any dose:

- results in death,
- is life-threatening (Life-threatening refers to an event in which the patient was at risk of death at the time of the event; it does not refer to an event, which, hypothetically, might have caused death if it were more serious.),
- requires inpatient hospitalization or prolongation of existing hospitalization,
- results in persistent or significant disability/incapacity,
- is associated with congenital abnormality/birth defect, or
- is another important medical event that may not be immediately life threatening or result in death or hospitalization but, based upon appropriate medical judgment are thought to jeopardize the patient or subject and/or require medical or surgical intervention to prevent one of the outcomes defining a SAE.

###### 6.3.1.1.4 Serious Adverse Reactions (SARs) and Suspected Unexpected Serious Adverse Reactions (SUSARs)

An AR that meets seriousness criteria, defined in Section 6.3.1.1.3, is defined as a serious adverse reaction (SAR). A suspected unexpected (unlisted) serious adverse reaction (SUSAR) is a SAR, the nature or severity of which is not consistent with the applicable product information (Investigator's brochure [IB]).

### 6.3.1.2 Classifications

#### 6.3.1.2.1 Severity

The severity of AEs will be classified using the modified graduation of the Common Terminology Criteria for Adverse Events (CTCAE V3.0)

- 0 = no event
- I = asymptomatic
- II = symptomatic, no treatment necessary
- III = symptomatic, specific treatment necessary
- IV = life threatening
- V = death

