#### 6.3.1.3.3 Other Procedures for Recording and Reporting Adverse Events

Events with class I and class II severity will be analyzed at the end of the trial period. Events with class III and class IV severity will be reported to the SMB. Details of the SMB are provided in Section 9.9. Class V events must surely be reported to the SMB.

During this study, there will be standard pharmacovigilance monitoring for SARs and SUSARs to allow for annual safety reporting procedures. The Sponsor (or delegate) will be responsible for safety updates to regulatory authorities in accordance with guidelines

and guidance and the German Medicines Act (AMG) and for updating IECs (Independent Ethics Committees) in accordance with the guidelines.

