#### *6.3.2.9 Unwanted Tissue Changes*

During cardiac MRI and echocardiography-examinations there will be a special check for unwanted tissue changes.

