The documentation to SMB contains detailed clinical information about the SAEs and the clinical course in written reports. Events with class III, class IV and V severity will be reported to the SMB. No member of the SMB will belong to Team A or B and all will be blinded to the randomization of the study treatment. If the SMB notes that the frequency of class III, IV and/or V events in the entire study or a given center exceeds that which is generally expected during CABG surgery, it will request unblinding of the affected patients. If SMB detects that the frequency of AEs exceeds the expected frequency irrespective of the study group allocation, it will review all cases with the local Investigators and determine adequate conduct of the study procedure. If the SMB notes the frequency of AEs exceeds the expected frequency only in the cell treatment group, it will unblind and review the data of the other study centers. Should the overall frequency of class III, class IV or class V AEs in the cell treated group be significantly ( $p < 0.05$  by chi-square test) higher than in the control group, the SMB will terminate the trial.

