## Appendix 2: Adverse Events of Specific Interest

| Adverse event reporting                                                                         |                          |                          |                                    |                                  |                          |                          |
|-------------------------------------------------------------------------------------------------|--------------------------|--------------------------|------------------------------------|----------------------------------|--------------------------|--------------------------|
|                                                                                                 | 0                        | I                        | II                                 | III                              | IV                       | V                        |
|                                                                                                 | no event                 | asymptomatic             | symptomatic, no specific treatment | symptomatic, treatment necessary | life-threatening         | death                    |
| AV block
 I  II  III |  |  |            |          |  |  |
| Prolonged QT-Interval                                                                           |  |  |            |          |  |  |
| Sinus bradycardia                                                                               |  |  |            |          |  |  |
| Supraventricular arrhythmia                                                                     |  |  |            |          |  |  |

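### The severity scale has no proper class for an asymptomatic, non-life-threatening event that needs treatment, so read literally it is class I and falls outside class-based SMB reporting and the termination comparison

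*Protocol*

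**What the plan says.** Section 6.3.1.2.1 of the Protocol sets out a modified CTCAE scale. Its lowest event grade is "I = asymptomatic", with no mention of treatment. Class II is a symptomatic event that needs no treatment. Class III is "III = symptomatic, specific treatment necessary". Class IV is "IV = life threatening" and class V is death. The grid in Appendix 2 for adverse events of specific interest repeats the scheme and heads its class III column "symptomatic, treatment necessary". Section 6.3.2.7 grades cardiac history in the same way.

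The class then decides what the Safety Monitoring Board (SMB) receives. Section 6.3.1.3.3 states "Events with class I and class II severity will be analyzed at the end of the trial period" and "Events with class III and class IV severity will be reported to the SMB", and adds class V. Section 9.9 repeats this: "Events with class III, class IV and V severity will be reported to the SMB". The same section bases termination on the overall frequency of class III, IV or V events, compared between cell-treated and control patients by chi-square test at p < 0.05.

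Some of the risks listed in section 1.3 are sought by instrument. Holter recordings (6.3.2.4) look for arrhythmia. During cardiac MRI and echocardiography, "there will be a special check for unwanted tissue changes" (6.3.2.9).

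**The concern.** Symptoms and need for treatment are separate properties of an event, and the scale merges them. Because class III requires both, an event that is treated but causes no symptoms cannot be class III. If it is not life-threatening it cannot be class IV either. By the text it is class I, the grade shared with incidental findings that need nothing.

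This would be minor if the class were only descriptive. Here it controls routine SMB reporting and which events enter the termination comparison. Section 1.3 names ventricular arrhythmia, tumour formation and unwanted tissue formation as possible risks of the cell product. The protocol looks for them with Holter, MRI and echocardiography, so they can be found in a patient without complaints. Such a finding can need treatment and still be left out of the comparison meant to detect excess harm in the cell arm.

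**Working it through.** No calculation applies. The question is where the definitions send each kind of event.

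**Step 1: combinations and classes.** For an event that is neither life-threatening nor fatal, symptoms (no/yes) and need for treatment (no/yes) give 2 × 2 = 4 combinations. The scale offers three classes for them. Applying 6.3.1.2.1 and then 6.3.1.3.3 and 9.9:

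| Event | Class by the text | Sent to SMB by class | In termination comparison |
|---|---|---|---|
| No symptoms, no treatment needed | I | no | no |
| Symptoms, no treatment needed | II | no | no |
| Symptoms, treatment needed | III | yes | yes |
| **No symptoms, treatment needed** | **I (no other class fits)** | **no** | **no** |
| Life-threatening, with or without symptoms | IV | yes | yes |
| Death | V | yes | yes |

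The fourth row is the gap. The fifth row limits it: class IV carries no symptom condition, so a silent event judged life-threatening is reported and counted.

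**Step 2: routes that do not depend on class.**

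- *SAE documentation (9.9).* The SMB receives written clinical information on SAEs. The definition in 6.3.1.1.3 includes important medical events needing intervention to prevent a serious outcome. A silent treated event judged serious therefore reaches the SMB. Its class is unchanged, so it still does not enter the class III-V comparison.
- *Events of specific interest (6.3.1.5, Appendix 2).* Listed events follow the SAE reporting procedure with no class condition. Ventricular arrhythmia and pericardial effusion are on the list. That procedure runs from the investigator to the sponsor (6.3.1.3.2), and the text does not say that non-serious listed events go on to the SMB.
- *Interim safety look (8.8).* MACE, which includes ventricular arrhythmia, is examined once, on the first 70 patients. Tissue changes are not part of it.

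**Step 3: the two kinds of finding compared.** A silent treated ventricular arrhythmia has the Appendix 2 route to the sponsor and the interim MACE look. A tumour or unwanted tissue change found on MRI or echocardiography has neither, because Appendix 2 does not list it and MACE does not include it. Under the protocol's stated reporting routes it reaches the SMB only if judged serious or graded III to V.

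**Step 4: direction.** Graded literally, the gap can only remove events from the class III-V count. It cannot add any.

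**The case against.** The strongest reply is that the gap is narrow and other safeguards surround it. Much of this stands. Life-threatening events are class IV with or without symptoms. Listed arrhythmias and effusions go to the sponsor under the SAE procedure. Many treated events would meet the SAE definition and so reach the SMB. Section 9.9 also gives the SMB a general duty to assess accumulating safety data, and its Charter, which is not at hand, may add triggers. None of these routes changes the class of an event, however, and the termination comparison is defined by class. The Charter could add reporting, but the protocol's scale and rule would remain as written.

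A reader might infer three stronger things that the documents do not support:

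- **That every silent event is class I.** Class IV contradicts this.
- **That the SMB never sees silent arrhythmias, or that they all wait until trial end.** The SAE and Appendix 2 procedures and the interim MACE look contradict this as a general statement.
- **That the rule can be shown to miss a particular excess, for instance of treated arrhythmias.** The rule uses the overall class III-V frequency, which in this population includes many other events after CABG. A comparison of arrhythmias alone is not the one that the protocol makes. The documents also give no rate of silent treated events from which a loss of sensitivity could be worked out.

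**Conclusion.** The point holds in a limited form. One combination, asymptomatic with treatment needed and not life-threatening, has no proper class and falls to class I. It is then left for end-of-trial analysis, is not reported to the SMB by class and is omitted from the termination comparison, even where the SMB learns of it as an SAE. Imaging-detected tumours and tissue changes are the most exposed.

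The size of the effect is unknown. Only the direction is clear: such events are undercounted in whichever arm they occur. The conclusion rests on a literal reading of the scale. Investigators may in practice grade a treated silent event as III, but the text does not permit that and grading could then differ between the seven sites. The correction is cheap and concerns the trial's termination rule, so it is worth making. The remaining routes keep it from being a failure of safety oversight as a whole.

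**What to change.** Reconcile the severity scale with the SMB reporting and termination text.

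- In 6.3.1.2.1 and the Appendix 2 grid, separate treatment from symptoms: I = asymptomatic, no treatment necessary; II unchanged; III = specific treatment necessary, with or without symptoms; IV and V unchanged. Align the cardiac history grades in 6.3.2.7 so that baseline and on-study grades mean the same.
- In 6.3.1.3.3 and 9.9, state that all SAEs, all Appendix 2 events and all unwanted tissue changes on MRI or echocardiography go to the SMB whatever their class. A tissue change that needs no treatment would still be class I and outside the comparison, but the SMB would see it.
- Section 6.3.1.4 also ties patient follow-up to classes II to IV. Re-grading would bring more events under it, so the sponsor should check that passage against the revised scale.

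The cost is protocol and CRF wording, re-grading of asymptomatic treated events already recorded, slightly more SMB reporting, and a somewhat higher class III rate in both arms. Re-grading should be done blind to treatment. No endpoint, eligibility criterion or sample size changes.

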#### 6.3.1.2.2 Causality of Adverse Events

The causality of AEs refers to the relationship of the AE to study treatment. When completing the CRF, the Investigator will be asked to assess the causality of the event. Causality will be categorized according to the following criteria:

- Not related:  
An adverse event which (according to the investigator's assessment) is not causally related to the use of the investigational medicinal product
- Unlikely (doubtful):  
An adverse event for which an alternative explanation is more likely, e.g. concomitant medication, concomitant diseases and/or the point at which the event occurred suggests that a causal relationship to the investigational medicinal product is unlikely
- Possible:  
An adverse event which might be caused by the use of the investigational medicinal product. An alternative explanation, e.g. concomitant medication, concomitant diseases, is inconclusive. The relationship in time is reasonable; therefore the causal relationship cannot be excluded
- Probable:  
An adverse event which might be caused by the use of the investigational medicinal product. The relationship in time suggests a causal relationship (e.g. confirmed by dechallenge). An alternative explanation (e.g. concomitant medication, concomitant diseases) is less likely
- Definite:  
An adverse event which is listed as a possible adverse reaction and cannot be reasonably explained by an alternative explanation (e.g. concomitant medication, concomitant diseases). The relationship in time (with the application of the investigational medicinal product) is very suggestive.

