## **5 STUDY TREATMENT**

### **5.1 Identity**

All patients enrolled in the study will undergo bone marrow aspiration (150-200 mL) and withdrawal of 20 mL blood one to two days before CABG surgery at Assessment Ia.

As there is only autologous application of the stem cells each patient is his own donor. Herewith the inclusion and exclusion criteria of the study population and the assessments describe the selection and testing of the donors.

For all patients CD133+ cells will be selected from the bone marrow aspirate. For patients randomized to the active treatment group the cells will be suspended in physiological saline + 10% autologous serum. For the patients of the control group, the CD133+ cells will be stored at the manufacturer. See Section 5.8 for further details of bone marrow aspiration and Section 5.9 for further details of CD133+ cell and placebo preparation and treatment.

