## **5.8 Bone Marrow Aspiration, Blood Collection and Transport**

All patients enrolled in the trial will undergo bone marrow aspiration from the iliac crest. The procedure will be carried out under local anesthesia one to two days before surgery (Day -2 to -1). In total 150 to 200 mL bone marrow will be harvested. The procedure will be performed by an experienced hematologist or surgeon within a qualified operating room according to §20b German Medicinal Products Act. Furthermore, 20 mL of peripheral blood will be drawn for preparation of autologous serum. The bone marrow aspiration, blood collection, packaging, labeling and transport to the cell processing laboratory will follow SOP's developed and validated by Miltenyi Biotec GmbH.

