### 6.3.1.3 Monitoring, Recording and Reporting of Adverse Events

#### 6.3.1.3.1 General Requirements

During the course of the study, all AEs (including SAEs), irrespective of the relatedness to the study drug, will be recorded on the AE pages of the CRF. During each monitoring visit, the Investigator and the monitor will review all AEs. The Investigator will be

responsible for ensuring that correct information concerning all AEs is included on the appropriate CRF forms.

The following data will be recorded:

- description of the AE: nature, frequency, intensity, time and date of onset and resolution, treatment, outcome, and causal relationship (in the opinion of the Investigator) to the study drug for each AE;
- whether the AE has to be considered as a SAE;
- action taken.

All AEs occurring during the study must be followed-up until the AE has completely resolved, stabilized or the sequelae can be assessed by the Investigator. In case of withdrawal the respective CRF has to be completed.

The results of additional diagnostic measures as the result of an AE, such as laboratory tests, ECG, angiogram, echocardiogram and MRI must be available at site and eventually copied on request.

A flow chart for the reporting of SAEs is shown in Figure 8.

[figure not shown]

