#### *6.3.1.5 Adverse Events of Specific Interest*

Events that are listed in Appendix 2 are considered to be of specific interest for the purpose of this study and are monitored in detail. Documentation and reporting of Adverse Events of Specific Interest will be according to the standard procedure of SAE reporting in Section 6.3.1.3.2. continuously up to study end and furthermore as safety follow up to Assessment VI after 24 months. After study termination (Assessment V, 6-Month Follow-Up) AEs not listed as AEs of specific interest will not be documented unless they are possibly, probably or definitely related to the investigational medicinal product or result in death. In case of seriousness all possibly, probably or definitely related AEs will be reported at Assessment VI, 24-Month Follow-Up.

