### **8.6 Safety Analyses**

Adverse events (AEs) and serious adverse events (SAE) (comp. Sections 6.3), will be listed summed by occurrence, severity (comp. Section 6.3.1.2.1), outcome, and causal relationship to treatment (comp. Section 6.3.1.2.2) and will be descriptively compared between the two treatment groups using Fishers exact test. Associated AE tables present the total number of patients reporting at least one specific event and the maximum severity grade (patients reporting more than one episode of the same event are counted only once by the maximum severity and highest causality). Special tables will be displayed for MACE (comp. Section 6.3.1.6) and for AEs leading to withdrawal.

In addition, summary tables with patient identification will be presented. The tables provide the numbers and percents of patients with AEs, and also include the subject identification in the table.

Separate summarizations of AEs by worst severity, and of SAEs and AEs that are likely related to treatment and AEs that are unlikely related to treatment (comp. Section 6.3.1.2.2) will also be provided. All AEs will be listed.

Descriptive statistics for laboratory parameters (comp. Table 1, Section 6.3.2.1) will be presented by treatment group and time point. For continuous laboratory parameters, changes from baseline to the other time points will be presented by treatment group and descriptive statistics will be calculated.

Values will also be presented according to the CTC categories. Values outside corresponding normal ranges will be displayed and tabulated.

A new abnormality is defined as an out-of-range value that was previously normal or a value that is initially out of range in one direction (either low or high) and becomes out-of-range in the opposite direction at the end of the period. A worsened abnormality is a value that was out of range at the start and became more abnormal during the period. Should the rate of new or worsened abnormalities be deemed excessive, further examination of the nature of the abnormalities will be performed.

Changes in vital signs (comp. Section 6.3.2.2) and electrocardiograms will also be examined for treatment group differences.

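### Adverse-event causality is rated only against the investigational product, so no planned output attributes complications of the trial-imposed bone marrow aspiration, which both arms undergo

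*Protocol*

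**What the plan says.** **Causality scale.** Protocol 6.3.1.2.2 opens with a broad object: "The causality of AEs refers to the relationship of the AE to study treatment". The level definitions that follow are narrower and refer to the investigational medicinal product (IMP). The lowest is "An adverse event which (according to the investigator's assessment) is not causally related to the use of the investigational medicinal product". Section 6.3.1.3.1 asks for one causality item, "causal relationship (in the opinion of the Investigator) to the study drug for each AE". Section 6.3.1.1.2 uses the same object: events judged as "having a causal relationship of possibly, probably or definitely related to the IMP qualify as ARs".

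**Aspiration.** Section 5.8 states: "All patients enrolled in the trial will undergo bone marrow aspiration from the iliac crest". The volume is 150 to 200 mL, taken one to two days before surgery. Section 4.5 places randomization after it. For control patients, section 5.1 says the selected "cells will be stored at the manufacturer".

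**Outputs.** Section 8.6 compares AEs between arms with Fisher's exact test and gives separate summaries of "SAEs and AEs that are likely related to treatment and AEs that are unlikely related to treatment". It also lists all AEs.

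**After month 6.** Section 6.3.1.5 leaves events that are not of specific interest undocumented "unless they are possibly, probably or definitely related to the investigational medicinal product or result in death".

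**The concern.** Section 1.3 says the indication for bypass surgery does not depend on the cell protocol, so the aspiration is an addition made by the trial. In practice the cells cannot be given without it, and its complications are therefore part of the burden of the therapy compared with surgery alone. A phase III safety report should be able to state how often they occur.

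The plan has two analytic routes to harm: the relatedness split and the arm comparison. The first asks about the product, which a patient with a harvest-site complication before surgery has not yet received. The second looks for a difference between two groups that both had the aspiration. What is at stake is attribution. The events reach the database, but no output says that the study procedure caused them.

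**Working it through.** The protocol states no figure on this point, so there is none to reproduce. The check sets sections side by side and then sizes the effect under stated assumptions.

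**Sections side by side**

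- Object of the rating: study treatment in the lead sentence of 6.3.1.2.2, the IMP in the level definitions, the study drug in 6.3.1.3.1, the IMP in 6.3.1.1.2. No level, recorded item or table covers a study procedure.
- Sequence: aspiration (5.8), then randomization (4.5), then injection during surgery (5.2). An event between aspiration and injection cannot result from use of the product. The levels left are *not related* and *unlikely*, and under 6.3.1.1.2 neither makes an adverse reaction.
- Exposure: all patients are aspirated (5.1, 5.8) and allocation is 1:1 (4.5), so the two arms are equally exposed.
- Month 24: 6.3.1.5 and 3.1 limit which AEs are documented. Section 7.2.6.3 can be read as documenting any AE or SAE since the last assessment.

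**Inputs for the size**

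- N = 142, 71 per arm (8.7): 60 / (1 − 0.15) = 70.6, rounded up to 71, times 2.
- Aspiration-complication rate p: not given. Assumed 1% to 20% and equal in both arms.

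**Formulas**

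- Expected number affected = 142 × p.
- Expected between-arm difference = p − p = 0.
- Probability of at least one event = 1 − (1 − p)^142.
- Chance of Fisher p ≤ 0.05: exact two-sided rejection probability, 71 per arm, same p in each.

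| Assumed p | Expected affected of 142 | P(at least one) | P(Fisher p ≤ 0.05) |
|---|---|---|---|
| 1% | 1.4 | 0.76 | 0.0001 |
| 2% | 2.8 | 0.94 | 0.0015 |
| 5% | 7.1 | > 0.999 | 0.014 |
| 10% | 14.2 | > 0.999 | 0.026 |
| 20% | 28.4 | > 0.999 | 0.032 |

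The last column is false signal only. It stays below 0.05 at every rate shown and carries no information about the size of p. The third column shows that such events would probably occur even at low rates.

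**What a procedure rating would give**

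With zero attributed events in 142, the exact upper limits are:

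- one-sided 95%: 1 − 0.05^(1/142) = 2.1%
- two-sided 95%: 1 − 0.025^(1/142) = 2.6%

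**The case against.** The strongest reply is that nothing is lost from the record. Section 6.3.1.3.1 records every AE whatever its relatedness, with nature and onset. SAE reporting starts at consent (6.3.1.3.2), and section 8.6 tabulates AEs by arm and lists them all. Section 7.2.2 records the time of harvest and section 9.1 retains the reporter's own terms. An analyst could therefore pick out an iliac-crest bleed by term and date and add the two arms together, and a pooled table is something an SAP could supply. Severe events also reach the Safety Monitoring Board, which may review frequency regardless of arm (9.9).

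Most of this stands, and it limits the point to attribution. It does not remove it. The causality scale and the recorded item are fixed in the protocol, and an SAP cannot recreate an investigator's judgement that was never asked for. Inference from term and date works for an iliac-crest haematoma. It works poorly for infection, anaemia or pain around bypass surgery. The Board's stated benchmark for severe events is what is expected in bypass surgery, which does not isolate the aspiration.

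It can also be argued that *study treatment* in the lead sentence covers the aspiration, which appears under treatment in the synopsis and in section 5. That leaves some ambiguity, but the level definitions and the recorded item point to the product.

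Three stronger readings are tempting and are not supported:

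- *Late harvest-site harm is never recorded.* An event with onset before month 6 is recorded and followed until it resolves or stabilizes (6.3.1.3.1, 6.3.1.4), and 7.2.6.3 can be read as capturing any AE at month 24.
- *The safety conclusion is shown to be too favourable.* The events remain in the overall AE and SAE counts of both arms, and no rate is given from which a bias could be derived.
- *The definition of the top causality level, which requires a listed reaction, hides harm.* Possible and probable events already qualify as adverse reactions, and no stated rule depends on reaching the top level.

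**Conclusion.** The point holds as a gap in attribution and tabulation, not in collection. As worded, complications of a trial-imposed procedure are rated not related or unlikely, fall outside the treatment-related summary, and have expected difference zero in the arm comparison. That zero holds at any complication rate if the rate is equal in the two arms, which follows from aspirating everyone before randomization.

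The number of patients concerned is not known from the protocol. At assumed rates of 1% to 10% it is about 1 to 14 of 142. The gap does not affect the primary efficacy analysis. This is a cheap improvement worth making, because the missing judgement cannot be fully recovered at the analysis stage.

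**What to change.** - **6.3.1.2.2 and 6.3.1.3.1:** add a second causality rating on the same five levels for relation to study procedures, naming the bone marrow aspiration and the injection procedure.
- **8.6:** tabulate procedure-related AEs pooled over both arms with an exact confidence interval, as well as by arm. State whether the interval is one-sided or two-sided.
- **6.3.1.5:** extend the documentation rule after month 6 to events related to a study procedure.
- **6.3.1.5 and 3.1 against 7.2.6.3:** reconcile the restricted documentation in the first two with the wording of the third, which calls for any AE or SAE.

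The cost is one extra AE field for sites to complete, one extra table and the protocol wording. No new visit or test is needed.
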